## Abstract

**Background:**

Major depressive disorder (MDD) during pregnancy and postpartum depression are associated with significant maternal and neonatal morbidity. While antidepressants are readily used in pregnancy, studies have raised concerns regarding neurobehavioral outcomes in exposed infants. Omega-3 fatty acid supplementation, most frequently from fish oil, has emerged as a possible treatment or prevention strategy for MDD in non-pregnant individuals, and may have beneficial effects in pregnant women. Although published observational studies in the psychiatric literature suggest that maternal docosahexaenoic acid (DHA) deficiency may lead to the development of MDD in pregnancy and postpartum, there are more intervention trials suggesting clinical benefit for supplementation with eicosapentaenoic acid (EPA) in MDD.

**Methods/Design:**

The Mothers, Omega-3 and Mental Health study is a double blind, placebo-controlled, randomized controlled trial to assess whether omega-3 fatty acid supplementation may prevent antenatal and postpartum depressive symptoms among pregnant women at risk for depression. We plan to recruit 126 pregnant women at less than 20 weeks gestation from prenatal clinics at two health systems in Ann Arbor, Michigan and the surrounding communities. We will follow them prospectively over the course of their pregnancies and up to 6 weeks postpartum. Enrolled participants will be randomized to one of three groups: a) EPA-rich fish oil supplement (1060 mg EPA plus 274 mg DHA) b) DHA-rich fish oil supplement (900 mg DHA plus 180 mg EPA; or c) a placebo. The primary outcome for this study is the Beck Depression Inventory (BDI) score at 6 weeks postpartum. We will need to randomize 126 women to have 80% power to detect a 50% reduction in participants' mean BDI scores with EPA or DHA supplementation compared with placebo. We will also gather information on secondary outcome measures which will include: omega-3 fatty acid concentrations in maternal plasma and cord blood, pro-inflammatory cytokine levels (IL-1β, IL-6, and TNF-α) in maternal and cord blood, need for and dosage of antidepressant medications, and obstetrical outcomes. Analyses will be by intent to treat.

**Discussion:**

This study compares the relative effectiveness of DHA and EPA at preventing depressive symptoms among pregnant women at risk.

**Trial registration:**

Clinical trial registration number: NCT00711971

## Background

Major depressive disorder (MDD) is prevalent among women of childbearing age. Major depressive disorder is a significant cause of morbidity and mortality in the developed world, affecting 20-25% of women at least once during their lifetime[1]. The primary risk factors for MDD include female gender, family history of depression, and previous personal history of depression[2]. The World Health Organization estimates that MDD is among the top seven causes of disability-adjusted life years worldwide [3-5]. In a 30-year projection of mortality and disability by cause, Murray and Lopez found MDD to be a leading cause of disability-adjusted life years (years of potential life loss due to premature mortality plus years of productive life lost due to disability) for women globally[4].

Depressive symptoms sufficient to disrupt functioning have been estimated to occur in 5-25% of women after delivery [6]. A cross-national review of the literature found the prevalence rates of postpartum depression to vary between 0.5% and 24.5%[7]. A cohort study of depressed mood during pregnancy and after childbirth, based on testing with the Edinburgh Postnatal Depression Scale (EPDS), found that 9.1% of women scored above the threshold for probable depression at 8 weeks postpartum [8]. Postpartum depression is associated with significant functional impairment and with problems in maternal-infant attachment [9]. Despite the emphasis given to postpartum depression, antenatal depression may occur with an equal or greater prevalence. A recently published systematic review estimating the point prevalence of depression during pregnancy found prevalence rates for depression in the first, second, and third trimesters of pregnancy of 7.4%, 12.8% and 12.0%, respectively [9]. Likewise, a cohort study of 9,028 British women found that the prevalence of depression at 32 weeks gestation was 13.5% and actually exceeded the 9.1% depression prevalence at 8 weeks postpartum[8].

Treatment of depression during pregnancy raises mothers' and physicians' concerns regarding fetal safety. Many mothers ultimately express reluctance to take medications during gestation. Indeed, in a population screening study conducted among pregnant women attending antenatal clinics at our own institution, only 14% of those with a positive depression screen received any formal treatment for depression[10]. Women with a history of postpartum depression in a previous pregnancy have a 25-50% risk of depression recurrence [11]. Complications such as preterm birth, preeclampsia, need for cesarean delivery, and poor pregnancy outcome may be increased in women experiencing depression during pregnancy[12]. Women who experience depression during pregnancy are also at increased risk for persistence or worsening of depression in the postpartum period[9].

Depression during the critical period of mother-infant attachment may also adversely affect child neurodevelopment. In a review of the literature concerning infants of mothers suffering from postpartum depression, Grace and colleagues found that children of mothers experiencing postpartum depression performed less well on cognitive tasks than children on non-depressed mothers at 18 months[13]. Differences in language skills and Piaget's object concepts tasks were noted in particular and these effects were more pronounced in boys than in girls. In addition, the authors found that postpartum depression exerted a modest effect on child behaviors up to 5 years of life, including distractibility, and antisocial and neurotic behavior at home and in school[13].

Selective serotonin uptake inhibitors (SSRIs) are the standard treatment for antenatal and postpartum depression and are widely prescribed during and after pregnancy[14]. Some, but not all, observational studies have noted an increased risk for congenital cardiac malformations or pulmonary hypertension with this use of these medications[15]. SSRIs readily cross the placenta; Hendrick *et al *demonstrated that antidepressant and metabolite concentrations were detectable in 87% of cord blood samples of infants of mothers who had received SSRIs [16]. Although neonatal blood levels were below maternal drug levels, the effects of these compounds on the developing brain remain unknown. In a prospective study of newborn neurobehavior, Zeskind demonstrated that newborns that had been exposed to SSRIs in utero had increased motor activity and tremulousness when compared to unexposed neonates [17]. Exposed neonates also exhibited fewer changes in behavioral states and fewer different behavioral states. Changes in the proportion of rapid eye movement sleep were also noted. In another study of infants born after SSRI exposure in utero, Oberlander and colleagues observed that neonatal acute pain response was altered by exposure to SSRIs [18]. Although these observations are of uncertain clinical significance, they indicate that neurobehavioral changes are associated with SSRI exposure in utero [19].

In a meta-analysis of available studies on SSRI use during pregnancy and effects on the fetus and newborn, Lattimore et al found that infants exposed to SSRIs in utero are more likely to be low birth weight and more likely to be admitted to a SCN/NICU at birth than infants born to mothers not on these medications[20]. Sanz and colleagues have analyzed a database of reports of neonatal withdrawal symptoms [21]. Paroxetine was associated with neonatal convulsions and cases of neonatal withdrawal were reported after exposure to all SSRI drugs. Based upon these data, Ruchkin and Martin recommended that the threshold for prescribing these compounds during pregnancy and in the postpartum should be raised[22]. Concerns about these compounds have also led to an interest in complementary and alternative methods of preventing or treating MDD.

Omega-3 fatty acids, most frequently from fish oil, are one such complementary and alternative medicine method. There is a heterogenous literature surrounding the use of omega-3 fatty acids for mood disorders. Published systematic reviews of omega-3 fatty acids for monotherapy or adjunctive therapy of MDD in non-pregnant populations have reached conflicting conclusions regarding efficacy and called for further research[23-25]. While systematic reviews of trials of omega-3 fatty acids in affective disorders by Freeman, [23] Lin, [25] and Appleton, [26] found that supplementation produced statistical improvement in mood symptoms, these authors' analyses found considerable between-study heterogeneity, possibly due to differences in the populations studied, timing of administration, and differing proportions of the two main omega-3 fatty acids, eicosapentaenoic acid (EPA) and docosahexaenoic acid (DHA) in the fish oils studied.

Likewise, although omega-3 fatty acids might offer an alternative to SSRIs for antenatal and postpartum depression, there has been conflicting evidence of efficacy from the available clinical trials. In a recent systematic review of placebo-controlled trials of omega-3 fatty acids for prevention or treatment of perinatal depression, Jans *et al *did not find benefit for omega-3 supplementation in their total analysis. However, there was some evidence of effectiveness among women with MDD[27]. A recent large placebo-controlled randomized controlled trial (RCT) of DHA for prevention of perinatal depression among pregnant women not selected by risk status did not show a benefit of DHA for this indication[28].

One possible reason for the heterogeneity of results of the available trials may be differing effectiveness of DHA and EPA. Two systematic reviews of published RCT's have found EPA but not DHA to be effective in alleviating depressive symptoms[29,30]. Thus the Omega-3 fatty acids subcommittee assembled by the Committee on Research on Psychiatric Treatments of the American Psychiatric Association has called for further randomized controlled trials of omega-3 fatty acids for mood disorders, and in particular comparisons of EPA and DHA [23]. To our knowledge, the proposed study is the first to directly compare EPA and DHA-rich fish oils in a pregnant population.

## Methods

### Aims

The aim of this study is to determine whether EPA or DHA will prevent pregnancy-related depressive symptoms. We hypothesize that EPA-rich fish oil supplementation and DHA-rich fish oil supplementation will reduce the risk of antenatal and postpartum depressive symptoms in women who are at elevated risk for depression based on a previous history of major depressive disorder, a previous history of postpartum depression, or an Edinburgh Postnatal Depression Scale (EPDS) score between 9 and 19 in early pregnancy. The study will also directly compare the effects of EPA and DHA on depressive symptoms as measured by the Beck Depression Inventory score. In addition we hypothesize that fewer pregnant women assigned to the fish oil supplementation will require treatment with antidepressant medications and if medicated, a lower total dose will be required than for women receiving placebo. We will recruit pregnant women who are between 12-20 weeks gestation and will follow them through their pregnancies and up to 6 weeks postpartum. The women participating in this study will be receiving prenatal care at two health systems in southeastern Michigan, the University of Michigan Hospitals and Clinics and St. Joseph Mercy Health System/Integrated Health Associates. These health systems are located in Ann Arbor, Michigan and Ypsilanti, Michigan and the surrounding communities.

This study also has three secondary aims that will generate preliminary data on possible mechanisms of action of EPA and DHA in mental health. First, we will examine the relationship between EPA and DHA, maternal plasma fatty acid levels, and symptoms of depression. Second, we will explore whether EPA and DHA reduce depressive symptoms by reducing synthesis of pro-inflammatory cytokines IL-6, IL-1β, and TNF-α. Third, we will examine the relationship between EPA and DHA and standard pregnancy outcomes, including birth weight and length of gestation.

### Participants/Eligibility Criteria

To be eligible to participate in the study, women must be 18 years of age or older, have a confirmed, live, intrauterine pregnancy of greater than 12 weeks gestation but less than 20 weeks gestation, and be enrolled in prenatal care at one of the two participating health systems. They must be planning to deliver at one of the two participating hospitals and plan to remain in the southeastern Michigan area through 6 weeks after delivery. To qualify for the study, women must be at risk for depression, based on (i) a history of MDD, (ii) a history of postpartum depression, or (iii) an EPDS score between 9 and 19.

Women will be excluded from participating in the study if they are currently taking an omega-3 fatty acid supplement; taking antidepressant or other psychiatric medications; using therapeutic or prophylactic anticoagulation medication; or consuming more than 2 fish meals per week. In addition, pregnant women with a diagnosis of current major depressive disorder, or other psychiatric diagnoses, including current substance abuse, schizophrenia, and bipolar disorder will be excluded from study. Pregnant women with a history of bleeding disorder such as von Willebrand's Disease will also be excluded.

### Recruitment, Randomization, and Collection of Baseline Data

Screening for depression using the EPDS screen is carried out as standard clinical practice at most, but not all, of the participating clinical care sites. Clinicians caring for pregnant women use the EPDS to identify women at risk and to facilitate mental health referrals. We will identify our eligible population of women with EPDS 9-19 or a past history of MDD through a variety of mechanisms, including health care provider referrals, advertisements, a pregnancy and mental health research registry, and a screening questionnaire and "permission to determine eligibility" form administered at the time of visits to the obstetrician or midwife, or to an obstetrical ultrasound unit.

The EPDS is a widely used, valid and reliable 10 item measure of perinatal mood[31]. This scale was chosen because it is less reliant on somatic complaints than other depression scales, and somatic complaints are very common in normal pregnancy. The EPDS is self-administered and may be scored by a wide range of health care workers. The EPDS has also been shown to be responsive to mood changes as a function of treatment[32]. A cut off score of 12 has been recommended for detecting the presence of MDD, with sensitivities found to be .68 - 1.0 and specificities of .49-1.0[33]. EPDS scores above 9 may indicate subclinical depression and risk for later development of MDD[34].

Those eligible women who agree to be contacted will be given information about the study, and offered study participation. All eligible women are informed of the risks and benefits of study participation, and reminded that study participation is voluntary. Full written informed consent will be solicited. Women who agree to participate will undergo a final determination of eligibility with administration of the Mini International Neuropsychiatric Interview (MINI), either by phone or in person. The MINI will identify women with current MDD or other major psychiatric diagnoses or substance dependence. These women are not eligible for the study and will be excluded from the sample population prior to randomization. They will be offered referral information for appropriate mental health care. Women meeting all eligibility criteria will be randomized and will attend 4 study visits.

Randomization will be carried out by use of a random number table maintained in the University of Michigan Investigational Drug Service (IDS). The research team will be blinded to the results of the randomization. The research team will provide the IDS staff with a list of unique identifying numbers prior to the start of recruitment and, at the time of randomization, will inform the staff of the study identification number of each participant to be randomized. The IDS staff will then randomize participants to one of three study arms using a random number table: intervention #1, intervention #2, or placebo and will maintain randomization records until the last participant has completed the protocol.

The IDS will dispense all study supplement which will consist of either: a) EPA-rich fish oil supplement (1060 mg EPA plus 274 mg DHA) (intervention #1); b) DHA-rich fish oil supplement (900 mg DHA plus 180 mg EPA) (intervention #2); and c) a placebo (control arm). Because the EPA and DHA capsules are not identical in appearance, all subjects will receive some placebo capsules. For the EPA group, this will involve taking 2 large EPA capsules and 4 small placebo capsules daily; the DHA group will take 2 large placebo capsules and 4 small DHA capsules daily. The placebo group will take 2 large placebo capsules and 4 small placebo capsules daily.

The intervention supplements and placebo have been provided by *Nordic Naturals *in Watsonville, California. The EPA-rich fish oil (*ProEPAXtra*, *Nordic Naturals*, Watsonville, CA) planned as intervention #1 in this study contains an approximate 4:1 ratio of EPA to DHA (1060 mg EPA plus 274 mg DHA). The DHA-rich oil (*ProDHA*, *Nordic Naturals*, Watsonville, CA) to be studied as intervention #2 contains DHA and EPA in an approximate 4:1 ratio (900 mg DHA plus 180 mg EPA). We chose these fish oil supplements because of their EPA-rich and DHA-rich compositions. The control group (intervention #3) will receive a placebo that will contain 98% soybean oil and 1% each of lemon and fish oil and will be indistinguishable in appearance and taste from the active supplements. The supplements will be molecularly distilled and free of industrial contaminants, mercury, and organochlorines.

### Study Visits

As much as possible, the four study visits will be coordinated with the subjects' routine prenatal care or ultrasound appointments. Visit #1 will occur between 12 and 20 weeks' gestation. Full written informed consent will be obtained. Baseline demographic and past medical and obstetrical history data will be collected. The baseline BDI (Beck Depression Inventory) will be administered. After a 3-hour fast, subjects will have their blood drawn to measure their baseline omega-3 fatty acid and proinflammatory cytokine levels (IL-1β, IL-6, and TNF-α). Subjects will be given a 3 month supply of the study supplement at this visit. Subjects will be instructed to take three capsules twice daily with meals and to return all unused capsules to the research team at their next study visit.

The second study visit will take place between 26 and 28 weeks gestation. During this visit, the BDI will be completed and the MINI will be re-administered to assess for MDD, suicidal ideation and psychiatric co-morbidity. The subjects will return their prescriptions to the study staff and all unused capsules will be counted. A two month supply of the study supplement will be given to each subject.

The third study visit will take place between 34 and 36 weeks gestation. During this morning visit, the BDI will be completed and the MINI will be re-administered. In addition, a second fasting blood sample will be obtained to measure the participant's omega-3 fatty acid levels and proinflammatory cytokine levels (IL-1β, IL-6, and TNF-α). At this visit, a three-month supply will be dispensed in order to provide women with sufficient doses until the postpartum visit. Each participant will be provided with a packet containing sterile tubes for collection of cord blood. Participants will be instructed to bring this packet with them to the hospital when they present to the Labor and Delivery unit.

When the subject presents for delivery, clinical staff will be notified that the patient is a study participant. After delivery of the baby, cord blood will be collected and proinflammatory cytokine levels and fatty acid levels will be assayed (visit #4).

The final study visit will take place at the participant's 6 week postpartum check-up. During this visit, the BDI will be completed and the MINI will be re-administered. Participants will receive $20 and a parking voucher for each study visit that they attend.

Capsule compliance will be monitored by pill counts. Adherence to the study protocol will also be ascertained by measurement of omega-3 fatty acid concentrations in maternal plasma at baseline and at 34-36 weeks' gestation.

Study participants who score above at or above a 20 on the BDI or who meet criteria for MDD on the MINI at any time during the study period will be referred for appropriate management with a mental health provider, who may prescribe antidepressant medications if indicated. In this case, the participant will be instructed to continue with the study intervention during treatment and to complete all study visits. Any subject expressing suicidal ideation will be escorted to the psychiatric emergency department.

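### The supplement supplies stated in Study Visits do not span the visit windows stated there, so some fully adherent women would run out before visit 2 or visit 3

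*Protocol article*

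**What the plan says.** The Study Visits section of the protocol article gives each visit a gestational window and each dispensing a duration.

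- Visit 1: "Visit #1 will occur between 12 and 20 weeks' gestation", and "Subjects will be given a 3 month supply of the study supplement at this visit". The eligibility criteria set nearly the same limits: "intrauterine pregnancy of greater than 12 weeks gestation but less than 20 weeks gestation".
- Visit 2: "The second study visit will take place between 26 and 28 weeks gestation". Then: "A two month supply of the study supplement will be given to each subject".
- Visit 3: "The third study visit will take place between 34 and 36 weeks gestation". The BDI is completed and "a second fasting blood sample will be obtained to measure the participant's omega-3 fatty acid levels", along with cytokines. A further three-month supply is handed out, and the text says it is meant to last until the postpartum visit.

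The same section sets six capsules a day and has women bring unused capsules back at the next visit. It describes no carry-over, overage or interim resupply. It also uses maternal plasma omega-3 at baseline and at 34-36 weeks as an adherence measure. The Secondary Outcomes section lists the BDI at 26-28 and 34-36 weeks and the changes in plasma omega-3 and cytokines. The primary outcome is the BDI at 6 weeks postpartum.

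**The concern.** Each supply has to last until the next visit. The longest gap between visits 1 and 2, and between visits 2 and 3, exceeds the supply given at the start of it. A woman who takes every capsule and attends every visit on time could therefore spend days or weeks without supplement.

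The second of these gaps would fall directly before the 34-36 week sample. That sample is the biochemical adherence check, the source of the fatty acid and cytokine outcomes, and the only maternal sample taken on treatment. The BDI scores at 26-28 and 34-36 weeks are secondary outcomes, and they also enter the repeated-measures model under Multivariable Analyses. Time off supplement in the active arms would pull these contrasts toward no difference. A low plasma level caused by an exhausted supply could not be told apart from one caused by missed doses.

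**Working it through.** **Inputs.** Windows from Study Visits: visit 1 at 12-20 weeks, visit 2 at 26-28, visit 3 at 34-36. Supplies: 3, 2 and 3 months. The article does not define a month, so I take 84 to 92 days for three months and 56 to 62 days for two (28-day months up to calendar months). Central values are 91 days (13 weeks) and 61 days (8.7 weeks).

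The article gives no coverage figure to reproduce. Its only statement is that the third supply suffices, which step 3 tests.

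**Formula.** Longest interval = latest next visit − earliest current visit. Shortfall = interval − days supplied.

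**Step 1, visit 1 to visit 2.**
- Longest: 28 − 12 = 16 weeks = 112 days. Shortest: 26 − 20 = 6 weeks = 42 days.
- Largest shortfall: 112 − 92 = 20 days to 112 − 84 = 28 days. Eligibility requires more than 12 weeks, so these are limits approached rather than exceeded.
- With 13 weeks supplied, a woman enrolled before 26 − 13 = 13 weeks runs out whenever visit 2 is held. One enrolled before 28 − 13 = 15 weeks runs out if visit 2 is at 28 weeks. Across the month definitions these limits are 12.9 to 14.0 and 14.9 to 16.0 weeks.

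**Step 2, visit 2 to visit 3.**
- Longest: 36 − 26 = 10 weeks = 70 days. Shortest: 34 − 28 = 6 weeks = 42 days.
- Largest shortfall: 70 − 62 = 8 days to 70 − 56 = 14 days.
- Mid-window to mid-window, 35 − 27 = 8 weeks = 56 days, is covered. So is late to late, 36 − 28 = 8 weeks.

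**Step 3, visit 3 to postpartum.**
- Visit 3 at 34 weeks, birth at 40, check-up 6 weeks later: 46 − 34 = 12 weeks = 84 days, covered.
- Birth at 42 weeks, the article's post-term threshold: 48 − 34 = 14 weeks = 98 days, a shortfall of 98 − 92 = 6 to 98 − 84 = 14 days.
- With 13 weeks supplied, even a visit 3 at exactly 34 weeks needs a birth after 34 + 13 − 6 = 41 weeks.

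**Step 4, how many women.** Assume visit dates are independent and uniform within their windows (not in the documents).
- Visit 1 to 2: the share running out is (mean visit 2 − supply − 12)/8 = (27 − 13 − 12)/8 = 0.25. It is (27 − 12 − 12)/8 = 0.375 with 84 days and (27 − 13.14 − 12)/8 = 0.23 with 92 days. With t = visit 2 − 25, uniform on 1 to 3, the mean shortfall among those affected is [E(t²)/16]/0.25 = [(13/3)/16]/0.25 = 1.08 weeks.
- Visit 2 to 3: with c = supply − 8 weeks, the share is (2 − c)²/8. For 61 days, c = 0.714 and 1.286²/8 = 0.21. It is 2²/8 = 0.50 with 56 days and 1.143²/8 = 0.16 with 62 days. The mean shortfall among those affected is (2 − c)/3 = 1.286/3 = 0.43 weeks, or 3 days.

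**Step 5, pill counts.** At six capsules a day, 91 days is 546 capsules. A woman with a 112-day interval who takes all of them returns none. The count shows full use, although 112 − 91 = 21 days were uncovered.

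**The case against.** The strongest reply is that this is a journal article. A month's supply may be a nominal description, the investigational pharmacy dispenses everything, and bottle overage or interim refills may sit in the full protocol. For the first two supplies the article never says that they cover the longest interval. This has weight: overage or resupply would shrink or close the gaps, and the finding cannot claim that women did run out. But the point does not rest on missing detail. The article states specific durations and windows in one section, and they do not fit. It also has unused capsules returned, so leftovers from a short first interval are not described as available for a long second one.

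Four stronger readings are tempting, and the documents do not support them.

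- **Early enrolment depletes the supply before the 34-36 week sample.** It does not. A new supply is given at visit 2, and at least 34 − 28 = 6 weeks pass before visit 3. The pre-sample gap needs an early visit 2 followed by a late visit 3.
- **The primary outcome is diluted.** The supply before the 6-week postpartum BDI falls short only at the far end of gestation after an early visit 3.
- **Supply gaps would be counted as non-compliance.** Returned-capsule counts would show the reverse (step 5). Only a denominator of calendar days, which the article does not state, would give 546/672 = 81%.
- **Women in general would have gaps.** With 13 and 8.7 weeks supplied, roughly three quarters or more are covered in each of the first two intervals.

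**Conclusion.** The mismatch is real for the first two supplies. The shortfall is up to 20 to 28 days before visit 2 and up to 8 to 14 days before visit 3, and it persists under every reasonable meaning of a month. The third supply fails only in a corner case, at worst by 6 to 14 days.

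Under uniform visit dates, with supplies of about 13 and 8.7 weeks, some 25% of women run out before visit 2 and 21% before visit 3. The ranges over month definitions are 23-38% and 16-50%. Those shares depend on the assumed visit timing; the maximum shortfalls do not.

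The exposure is to secondary results: the BDI at 26-28 and 34-36 weeks, plasma omega-3, cytokines and the plasma adherence check. The likely direction is toward no difference between arms. Its size cannot be computed, because the article does not say how fast levels or symptoms change once supplement stops. All three arms face the same supply schedule, and randomization and the sample size are untouched.

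**What to change.** Reconcile the supply durations with the visit windows in Study Visits. Which of the two changes is for the sponsor to decide. If the full protocol already provides overage or interim resupply, one sentence in the article saying so would settle the matter.

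Separately, record the date on which each woman's supply ran out, so that days without supply can be told apart from missed doses when pill counts and the 34-36 week plasma levels are read.

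The cost is a wording correction, a matching dispensing or scheduling instruction, and one extra data field at each visit. The endpoints, analysis model and sample size stay as they are.
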